## Abstract

**Background:**

The consensus for the optimal treatment strategy for chronic Achilles tendinopathy (AT) is still debated and treatment options are limited. This results in a significant medical need for more effective treatment options.

**Objective:**

The aim of this study is to investigate the therapeutic effects of percutaneous bioelectric current stimulation (PBCS) on AT.

**Methods:**

A multicenter, randomized, double-blind, placebo-controlled clinical trial will be conducted. A total of 72 participants with chronic (ie, >3 months) midpoint AT will be randomized and receive four PBCS sessions—either verum or placebo—over 3 weeks. Both groups will complete daily Achilles tendon loading exercises in addition to the intervention. Evaluation sessions will be completed at baseline and during the intervention (weeks 0-3). Self-reported outcome measures will be completed at follow-up at weeks 4, 12, 26, and 52. The primary outcomes are the Victorian Institute of Sports Assessment–Achilles questionnaire scores and statistical evaluation of intraindividual differences between baseline and 12-week evaluations after initial treatment of verum therapy compared to control. Secondary outcomes will assess Pain Disability Index scores; average pain, using the 11-point Numeric Rating Scale; return to sports; and use of emergency medication.

**Results:**

The study began in May 2021. As of October 2022, we randomized 66 out of 72 participants. We anticipate completing recruitment by the end of 2022 and completing primary data analysis by March 2023.

**Conclusions:**

The study will evaluate the effects of PBCS on pain, physical function, and clinical outcomes.

**Trial Registration:**

German Clinical Trials Register DRKS00017293; https://tinyurl.com/mvz7s98k

**International Registered Report Identifier (IRRID):**

DERR1-10.2196/40894

## Introduction

Achilles tendinopathy (AT) is a painful overuse injury [1] and is particularly common in athletes. The prevalence of AT among runners is estimated to be between 6.2% and 9.5% [2], with the highest prevalence (83%) among middle-distance runners [3].

AT is caused by increased stress on the Achilles tendon, especially when running long distances in hilly terrain [4]. People older than 35 years are particularly susceptible [4] to AT. Most commonly, the pain and thickening of the Achilles tendon occur in the midportion of the Achilles tendon, especially 2 to 6 cm distal to the insertion of the Achilles tendon to the heel (ie, the calcaneus) [5].

Achilles tendons of patients with AT show advanced degeneration and changes in the arrangement of collagen fibers. Furthermore, there is ventral sprouting of new blood vessels and associated nerve endings [6]. These are considered the main cause of pain, although there are microscopic changes without clinical symptoms as well as clinical symptoms without microscopic changes. In this respect, the cause of the pain is not fully understood. Since these microscopic changes are considered as degenerative rather than inflammatory, the term tendinopathy is used instead of tendinitis [7].

The leading symptom of AT is load-dependent pain in the course of the Achilles tendon, usually associated with swelling. In the acute form, increasing pain occurs at the Achilles tendon a few centimeters above the heel over a period of a few days. The pain can be temporarily relieved by immobilization [8]. Manual examination of the Achilles tendon reveals that it is swollen, reddened, and hardened. Acute AT often progresses to a chronic course [9]. Symptoms may persist for months to years. The pain remains at about the same intensity with any type of exercise or sports activity, but increases when running uphill or climbing stairs. After resting or in the morning, the pain is especially severe because of stiffness and loss of elasticity of the Achilles tendon. Rupture or partial rupture of the tendon is a frequent complication.

AT is a clinical diagnosis based on localized tendon pain and swelling and pain with activities. Imaging, such as sonography or magnetic resonance imaging, can be used to assess tendon morphology and pathologic conditions.

Therapeutic options for AT are limited [1,10]. Current conservative treatment strategies involve the topical or oral application of nonsteroidal anti-inflammatory drugs (NSAIDs), loading exercises (ie, eccentric-concentric loading), cooling, taping, and exercise rehabilitation. Nonsurgical therapies are also used, including acupuncture, focused shock wave treatment, and electrotherapies (ie, different forms of transcutaneous electrical nerve stimulation [TENS]) [11-13]. In cases of long-standing symptoms that cannot be managed conservatively, surgical splitting of the tendon lengthwise and excision of necrotic tissue can be attempted [14]. However, studies show that the long-term results of surgical therapy do not differ from those of conservative therapy and that operative treatments have a higher risk of other complications [15]. The best evidence for treating AT is available for loading exercises (ie, eccentric-concentric loading) [16]; for all other forms of therapy, evidence is contradictory or anecdotal. Overall, it must be concluded that the optimal treatment strategies for chronic AT are still being debated and that treatments are protracted and mostly unsatisfactory. Given the high prevalence of unsatisfactory treatment options, there is a significant medical need for more effective treatment options.

Percutaneous bioelectric current stimulation (PBCS) treatment is a form of microinvasive electrotherapy different from the aforementioned TENS-like approaches. PBCS mimics and increases physiological electric fields to modulate local tissue inflammation and to trigger the regeneration of nerves, muscles, ligaments, and tendons.

In this study, PBCS using the DC Stimulator Mobile (original equipment manufacturer [OEM] version; Axomera-Molsberger), which has already shown promising results in the treatment of ligaments, tendons, and muscle tissue [17], will be compared to a control treatment without electrical output.

## Methods

### Study Design

This study is a randomized, double-blind, placebo-controlled multicenter trial.

Participants will be randomized to either the verum group or the control group. In addition to the intervention, participants in both randomization groups will receive the same baseline therapy in the form of tendon-loading exercise. Each participant will receive four treatment sessions within 3 weeks of inclusion. Evaluation sessions, where primary outcome data are collected, will be conducted at baseline (ie, inclusion) and at week 4. Self-reported follow-ups will be conducted at weeks 4, 12, 26, and 52 (Figure 1).

In this study, the medical device DC Stimulator Mobile (OEM version; Axomera-Molsberger) developed for PBCS treatment will be tested with regard to its technical and medical performance and safety. The aim is the statistical evaluation of therapeutic effects of PBCS with electrical output (verum) in participants with achillodynia compared to PBCS treatment without electrical output (control) as an additional benefit (ie, “add-on”) to an evidence-based standard therapy. This trial was retrospectively registered at German Clinical Trials Register (DRKS00017293) in February 2022.

**Figure 1 figure1:**
[figure not shown]
Flowchart of the study process. The verum group will receive PBCS treatment with electrical output as described above. The control group will receive PBCS treatment as described above with no electrical output: the current and voltage will be equal to zero. PBCS: percutaneous bioelectric current stimulation.

### Recruitment

Study participants will be recruited directly at the trial sites. Recruitment will be supported using posters, mass emails, and direct approach of potential participants at the study centers. Prior to inclusion in the study, each participant will be informed by the investigator about the nature, significance, risks, and scope of the clinical trial, as well as about the right to terminate participation in the study at any time without incurring any negative effects. Generally understandable information documents will be handed out.

Participants must be given a reflection period of at least 24 hours to decide whether to participate in the study. In addition, they must be given the opportunity to clarify any unanswered questions beforehand. Study-specific investigations to verify the inclusion and exclusion criteria will be performed after the participant has given legally effective consent to the study. Only participants who meet all inclusion criteria will be included and randomized into the SMART-TRIAL electronic data capture (EDC) platform. Participants who do not meet the eligibility criteria will be excluded.

The inclusion criteria will be as follows: achillodynia diagnosis confirmed by a consulting doctor, pain in the Achilles tendon approximately 2 to 7 cm from calcaneus insertion, pain intensity of at least 4 on the 11-point Numeric Rating Scale (NRS) on at least one day in the last 7 days before the start of treatment, aged 18 to 65 years, Achilles tendon pain for 3 or more months, adequate communication skills, and participant must be able to recognize the nature, significance, and scope of the clinical trial and to direct his or her will accordingly.

The exclusion criteria will be as follows: needle phobia; previous PBCS treatment or eccentric training, as specified in this study, of the affected Achilles tendon; Achilles tendon pain for more than 2 years; BMI greater than 30 (obesity grade I); in women, pregnancy; pain intensity of 9 points or higher on the 11-point NRS on any day in the last 7 days before the start of treatment; inability to technically perform the Victorian Institute of Sports Assessment (VISA); pending disability pension application; pacemaker; history of surgery on the Achilles tendon; cortisone injection to the Achilles tendon in the last 3 months; chronic pain of other etiology with ongoing pain management; anticoagulant therapy within 7 days before start of treatment—taking acetylsalicylic acid up to 100 mg/day is not an exclusion criterion; taking opiates within the last 4 weeks before start of treatment; history of taking fluoroquinolone, antibiotics, or statins within the past 6 months; analgesic, drug, or opiate dependence; alcoholism; local infection; type 2 diabetes; renal disease requiring dialysis; autoimmune disease; vascular disease; peripheral neuropathy; other nerve compression syndromes of the lower extremities; radiculitis; rheumatoid arthritis; Reiter syndrome; and other medical reasons as determined by the study physician.

### Randomization

Structural equality of both study arms will be achieved by randomization. Randomization will be performed using the randomization module of the SMART-TRIAL EDC platform. Allocation to the two study arms will be in the form of permuted blocks of variable length, stratified by study site in an allocation ratio of 1 to 1.

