### Sample Size

The sample size is calculated on the basis of the primary outcome, taking into account a clinically relevant effect size between verum and control.

In this study, the treatment effect is considered clinically relevant if the effect size between study arms is at least Δ/σ = 0.75.

To demonstrate a significant treatment effect in the primary statistical analysis with 80% power using a 2-sided Wilcoxon-Mann-Whitney test at the *α*=.05 level, a sample size of 62 participants in total is needed, with 31 participants per intervention group.

The allocation ratio is 1 (verum) to 1 (control). Assuming a dropout rate of 15%, a total of 72 participants should be included in the study.

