### Statistical Analysis

Statistical evaluation will generally be carried out using descriptive methods in the form of frequency tables and statistical parameters, such as means, SDs, and quantiles. As graphical procedures, bar charts will be created for qualitative data, and box-and-whisker plots will be created for quantitative data. In addition, inferential statistical analyses will be performed using appropriate significance tests and CIs. Missing values will not be replaced.

The primary statistical evaluation will be performed with a 2-sided Wilcoxon-Mann-Whitney test at the global significance level of *α*=.05; the results will be interpreted in a confirmatory sense.

The evaluation of the secondary evaluation criteria of efficacy will be performed with adequate 2-sided tests. Here, local levels (local level *α*=.05) will be controlled instead of the global significance level, and no adjustment will be made for multiple testing. *P* values of the secondary evaluation criteria will be interpreted descriptively only.

The safety evaluation criteria will be evaluated exploratively. In the exploratory evaluation of the safety criteria, adjustment for multiple testing would be counterproductive and will, therefore, not be performed.

For the primary target criterion, the following 2-sided test problem will be set up:

H_0_: *d*=0 versus H_1_: *d*≠0

where *d* indicates the effect size between intervention groups.

The null hypothesis is as follows: in the statistical evaluation of intraindividual differences between scores at start of treatment and at week 12, there will be no difference in the VISA-A score for symptom assessment between verum and control.

The research hypothesis is as follows: in the statistical evaluation of intraindividual differences between values at start of treatment and at week 12, there will be a difference in the VISA-A score for the assessment of symptomatology between verum and control.

For the secondary outcome of efficacy, corresponding 2-sided test problems will be set up and solved.

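### Randomisation is stratified by site but the confirmatory rank test ignores site, so to the extent that sites differ the test is conservative and forgoes some precision

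*Protocol article*

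**What the plan says.** The Randomization section of the protocol article describes the allocation thus: "Allocation to the two study arms will be in the form of permuted blocks of variable length, stratified by study site", in a 1:1 ratio.

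The Statistical Analysis section fixes the confirmatory test: "The primary statistical evaluation will be performed with a 2-sided Wilcoxon-Mann-Whitney test at the global significance level of" .05. The endpoint is each participant's change in VISA-A from start of treatment to week 12, compared between arms.

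The Sample Size section is built on the same test. It sets the target effect ("the treatment effect is considered clinically relevant if the effect size between study arms is at least Δ/σ = 0.75"), plans "with 80% power using a 2-sided Wilcoxon-Mann-Whitney test", and concludes that "a sample size of 62 participants in total is needed, with 31 participants per intervention group". It then allows for dropout: "Assuming a dropout rate of 15%, a total of 72 participants should be included in the study".

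Neither the Sample Size section nor the Statistical Analysis section mentions site, a stratified test or any covariate. The article gives no number of sites and no between-site variance.

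**The concern.** Permuted blocks within site force the two arms to be nearly balanced at every site. A difference between sites in mean VISA-A change therefore largely cancels out of the comparison between arms. A test that does not know about site still counts that variation as noise. Its reference distribution is then too wide for the randomisation actually used: the real type I error falls below 5%, and a true effect is somewhat harder to detect than it need be.

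At stake is a little power in a trial planned with 62 evaluable participants. The size of the loss depends entirely on how much sites differ in mean change, which the article does not say.

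**Working it through.** **1. The plan's own figure.** Inputs from the Sample Size section: Δ/σ = 0.75, two-sided α = .05, power 80%, 1:1 allocation. I used the two-sample noncentral t power with the effective n per arm multiplied by 3/π, the asymptotic relative efficiency of the Wilcoxon-Mann-Whitney test for normal data.

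- 30 per arm: effective n = 30 × 3/π = 28.65; noncentrality = 0.75 × √(28.65/2) = 2.84; power 79.6%.
- 31 per arm: effective n = 31 × 3/π = 29.60; noncentrality = 0.75 × √(29.60/2) = 2.89; power 81.0%.

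So 31 per arm, 62 in total, reproduces. Nothing in that calculation uses site.

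**2. Direction and limiting size.** Let the total variance of the change be σ² and the site share be ICC. With perfect balance within sites, the variance of the difference between arms is 4σ²(1 − ICC)/N. A test that ignores site works with about 4σ²/N. The true standard error is thus √(1 − ICC) times the one used, and the actual type I error is approximately 2 × [1 − Φ(1.96/√(1 − ICC))]:

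- ICC 0.05: 1.96/0.975 = 2.01, giving 4.4%
- ICC 0.10: 1.96/0.949 = 2.07, giving 3.9%
- ICC 0.20: 1.96/0.894 = 2.19, giving 2.8%

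Incomplete blocks and a small number of sites soften this, so it is a guide to direction and order of size only.

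**3. Simulation.** Assumptions, none of them given in the article: blocks of 2 and 4 within site; normal outcome with total SD 1; three layouts of 62 participants (4 near-equal sites; 8 near-equal sites; 6 unequal sites of 30, 14, 8, 5, 3 and 2); ICC from 0 to 0.30. There were 6000 runs per scenario, so the Monte Carlo standard error is about 0.003 for type I error and 0.005 for power. Power is at Δ/σ = 0.75. Ranges are over the three layouts.

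| ICC (assumed) | Type I error, plain test | Power, plain test | Power, site-aligned rank test | Power, van Elteren |
|---|---|---|---|---|
| 0 | 0.044-0.049 | 0.81 | 0.81 | 0.77-0.79 |
| 0.05 | 0.048-0.050 | 0.81 | 0.82 | 0.78-0.80 |
| 0.10 | 0.041-0.044 | 0.82-0.83 | 0.84 | 0.80-0.82 |
| 0.20 | 0.032-0.039 | 0.84 | 0.88-0.89 | 0.85-0.87 |
| 0.30 | 0.026-0.027 | 0.84-0.87 | 0.91-0.92 | 0.88-0.91 |

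Both tests that use site hold a type I error of 0.047-0.054 throughout. A separate simulation gave, for the plain test, about 4.2-4.4% at ICC 0.05, 3.8-4.6% at 0.10 and about 3.4% at 0.20. Pooling the two gives 4.2-5.0%, 3.8-4.6% and 3.2-3.9%.

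**4. Gain from using site, rank test against rank test** (site-aligned minus plain; 4, 8 and 6 sites in turn):

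- ICC 0.05: 0.823 − 0.814, 0.821 − 0.814, 0.820 − 0.812, about 1 point
- ICC 0.10: 0.840 − 0.821, 0.844 − 0.822, 0.841 − 0.827, about 1-2 points
- ICC 0.20: 0.884 − 0.840, 0.886 − 0.841, 0.884 − 0.843, about 4-5 points

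**5. Planned power.** The lowest simulated power of the plain test in any scenario was 0.804 (4 sites, ICC 0.02), because the planning σ is read as the total SD, site variation included.

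**The case against.** The strongest reply is that nothing here is invalid. The test is prespecified, its type I error is at or below the nominal level, and the planned power is met. The endpoint is a within-patient change, which already removes stable site differences in baseline level. At ICC 0.05 or less the loss is negligible. The article is condensed, and the statistical analysis plan, which is not shown, may add a site-adjusted sensitivity analysis. All of this stands except the last point as a full answer. The article itself names the confirmatory test and sizes the trial on it, so ignoring site is a stated choice. Change from baseline also does not remove site differences in response.

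Four stronger readings are tempting and are not supported.

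- A reader might infer that the test certainly runs below 5% and that power is lost. That needs a material between-site variance, and the article gives none.
- A reader might infer that practice differs by site. Interventions and Blinding ties the number of needles to the extent of the painful area in each participant. Recruitment lists several routes without saying that they vary by site. Differences in exercise coaching are not mentioned. Limitations does say that the practitioner locates the sensitive points and that needling itself may have effects in both groups. Site effects on response are therefore possible, but not documented.
- A reader might compare the plain rank test with a linear model that includes site and credit the whole power gain to site. With no site variance at all, such a model already gains about 2 points on normal data (79.7% to 81.9%, and 81.1% to 82.9%, in two layouts). That part is the switch from a rank test to a parametric one.
- A reader might take the van Elteren test as the automatic remedy. At ICC 0 with 8 sites it has 0.77 power against 0.81 for the plain test, and it is clearly better only from about ICC 0.20.

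**Conclusion.** The mismatch is real: the allocation is stratified by site and the confirmatory test does not use site. Its consequence is conditional and modest. At ICC 0.05 it barely matters, at 0.10 it costs 1-2 points of power, and at 0.20 it costs 4-5 points. These figures rest on assumed site layouts, block sizes and ICCs, on normal outcomes and on 62 evaluable participants.

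This is a point of efficiency and consistency with the design. It is not an error of validity, nor a shortfall against the planned 80% power.

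**What to change.** Before unblinding, make the primary analysis account for site, in one of two ways:

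- keep a rank test, but use a site-aligned (stratified) version; or
- model week-12 VISA-A with treatment, site and baseline VISA-A.

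With either, fix a rule for pooling very small sites. Use van Elteren only if sites are few and none is small. If the plain test is kept, state why site is left out.

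The cost is wording, a pooling rule and a few degrees of freedom; no further participants are needed. At ICC 0 the site-aligned rank test lost essentially nothing (0.81 against 0.81). The model would replace a comparison of ranks with one of means, so it should be recorded as a deliberate change to the primary analysis. The Results section reports 66 of 72 randomised as of October 2022, with primary data analysis still ahead, so at publication there was time for this.

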### Interventions and Blinding

Four mandatory PBCS treatments will be performed within 3 weeks after inclusion. There must be at least 2 days between treatments.

Depending on the extent of the painful area, 2 to 8 stainless steel needles (0.20-0.3 mm) will be used. Each needle will be inserted into the affected (ie, paratendinous) tissue until the participant feels the tip of the needle exactly at the painful area. The needle will then be withdrawn a few millimeters so that the tip of the needle is as close as possible to the painful area. The needle probes will be individually connected to the PBCS stimulator via clips and flexible cables. PBCS direct current stimulations will then be performed over 30 minutes according to the indication-specific stimulation protocol; electrical signals will be of the order of 140 mV/ mm, and the drive current will be approximately 20 to 50 μA/cm (Figure 2).

Double-blinding is ensured by the identical design of the treatment hardware. One of the connection cables, however, is technically modified in such a way that no current will be conducted, thus generating no electrical stimulation. The difference in the connection cables will not be detectable by either investigator or participant. The success of blinding will be additionally measured using a blinding question after the first treatment: the participant will be asked whether he or she thinks that he or she has been treated with or without electrical stimulation.

**Figure 2 figure2:**
[figure not shown]
Intervention with PBCS therapy. PBCS: percutaneous bioelectric current stimulation.

### Outcome Measures

#### Primary Outcome

The VISA–Achilles questionnaire (VISA-A) score [18] will be used as the primary outcome measure. Intraindividual differences between values at baseline and values 12 weeks after initial treatment with verum therapy compared to control will be evaluated. The VISA-A questionnaire is an index of the severity of a clinically diagnosed condition (ie, AT). It contains eight questions on three domains of pain, function, and activity. Scores are summed to a total with a maximum of 100. In this study, the German adaptation (VISA-A-G) will be used. The VISA-A-G questionnaire was tested for reliability, validity, and internal consistency [19].

